**3.3 Study endpoints**

*Primary endpoint*

Primary objective of the study will be to explore prognostic factors correlated with rate of 2 years PFS. PFS is defined as time from end of salvage treatment performed at first relapse to documented biochemical progression or radiological progression (or both), death from any cause or censoring at date of last follow-up. Biochemical progression is defined as the date in which a PSA increase above 0.2 ng/ml for patients with a PSA nadir < 0.2 ng/ml or 2 consecutive PSA increases >25% if compared to nadir in patients with a PSA nadir > 0.2 ng/ml is detected. Radiological progression will be defined as the occurrence of any new lesion detectable with PSMA PET/CT and/or any other molecular/radiological exam, which will be performed in case of biochemical or clinical progression

*Secondary endpoints*

- Explore prognostic factors correlated with Overall survival (defined as time between end of tailored treatment after 68Ga-PSMA PET/CT and death)

- Explore prognostic factors correlated with Cause specific survival, defined as time between end of tailored treatment and death for prostate Cancer

- Explore prognostic factors correlated with Radiological PFS, defined as the occurrence of any new lesion detectable with PSMA

PET/CT and/or any other molecular/radiological exam, which will be performed in case of biochemical or clinical progression

-Record rate of patients with impaired quality of life measured by EORTC QLQ-C30 and EORTC QLQ-PR25 at 2 years (defined as decrease by 10 points in global health scale and functional scales or increase by 10 points in symptoms scales compared with baseline, without later improvement superior by 10 points)

-To assess the proportion of management changes induced by positive PSMA PET/CT results

-To assess the association between PSMA PET/CT detection rate and baseline detection of a specific panel of miRNA (miR-186, miR-26a, miR-374a, miR-410, miR-660)

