**6. STUDY EVALUATIONS**

**6.1 Pre­Treatment Evaluation**

Baseline evaluations include:

- - demographics data;
  - active co­morbidities and current medical treatments;
  - Pathological staging, margin status, PSA value and Gleason Score at the time of prostate cancer diagnosis;
  - previous treatments for prostate cancer;
  - Baseline PSA at BR
  - Imaging procedures:
- Staging with PSMA PET/CT
  - assessment of Performance Status with the Eastern Cooperative Oncology Group (ECOG) Score;
  - Baseline Quality of life assessment measured by EORTC QLQ-C30 and EORTC QLQ-PR25 (baseline evaluation should be performed before radiotherapy beginning);
  - Blood samples to detect baseline expression of a specific panel of miRNA (miR-186, miR-26a, miR-374a, miR-410, miR-660)
  1. **Evaluation During Treatment**

Patients will be evaluated as follows:

- After initial PSMA PET/CT, treatment modalitywill be recorded to assess the proportion of management changes induced by positive PSMA PET/CT results
- every 3 months from therapy start with ECOG Score EORTC QLQ-C30 and EORTC QLQ-PR25
- PSA value every 3 months from therapy start
- PSMA PET/CT will be repeated in case of biochemical progression, defined as a PSA increase above 0.2 ng/ml for patients with a PSA nadir < 0.2 ng/ml or 2 consecutive PSA increases >25% if compared to nadir in patients with a PSA nadir > 0.2 ng/ml is detected.

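### PFS is censored at the last follow-up rather than the last PSA, so a patient who stops PSA but stays in contact is credited with progression-free time that was only partly observed

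*Protocol*

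**What the plan says.** Protocol section 3.3 runs PFS from the end of salvage treatment "to documented biochemical progression or radiological progression (or both), death from any cause", and the sentence closes with "death from any cause or censoring at date of last follow-up". The date of last follow-up is not defined anywhere in the protocol.

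Biochemical progression rests on PSA values alone. One branch is "a PSA increase above 0.2 ng/ml for patients with a PSA nadir < 0.2 ng/ml"; the other is two consecutive rises of more than 25% over the nadir. Radiological progression is a new lesion on PSMA PET/CT or another examination, "which will be performed in case of biochemical or clinical progression".

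The schedule is in section 6, under Evaluation During Treatment. One item is "PSA value every 3 months from therapy start". A separate item is contact "every 3 months from therapy start with ECOG Score EORTC QLQ-C30 and EORTC QLQ-PR25". A third states that "PSMA PET/CT will be repeated in case of biochemical progression". No routine imaging is planned.

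Section 2 adds a 48-month phase of 3-monthly checks whose content is not given. Section 3.3 also lists overall survival as a secondary endpoint, and a further one is to "Explore prognostic factors correlated with Cause specific survival, defined as time between end of tailored treatment and death for prostate Cancer".

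**The concern.** A censoring date for PFS should be the last date on which the patient was known to be free of progression. Here that knowledge comes mainly from PSA. Once PSA testing stops, biochemical progression cannot be declared, and the usual trigger for a repeat PET is lost too.

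The quality-of-life and performance-status contacts are listed apart from PSA, and the survival endpoints need only vital status. A last contact later than the last PSA is therefore possible under this plan. Take a patient whose last PSA is at 9 months and who is known to be alive, with no recorded event, at 30 months. Under the stated rule this patient is a 2-year success.

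Two things are at stake. The 2-year PFS estimate would lean upward. And the primary endpoint concerns prognostic factors for 2-year PFS, so a factor that goes with poorer PSA adherence could look protective with no true effect. A larger sample would not remove either bias.

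**Working it through.** **The plan's own figure.** Section 6.3 assumes 2-year PFS of 80%, a 6-point margin and a 95% interval. n = 1.96² × 0.80 × 0.20 / 0.06² = 170.7, so 171 against the stated 172. With 5% drop-out, 171 / 0.95 = 180, as stated. The sample size is not in question here; its 80% and 6 points serve as the reference.

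**Assumptions for the bias.** From the protocol: S(24 months) = 0.80 and PSA every 3 months. Assumed, because the protocol is silent: a constant hazard; a share f of patients who stop PSA at a random time within 24 months, unrelated to prognosis, but stay in contact beyond 24 months; and no other early censoring.

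**One patient.** With the last PSA at 9 months and no progression by then, the chance of progressing between 9 and 24 months is 1 − 0.80^(15/24) = 0.13. The stated rule sets this to zero unless clinical imaging or death reveals an event.

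**The cohort.** With everyone in contact past 24 months, the Kaplan-Meier estimate under the stated rule is 0.80 + f × h, where h is the average probability of an unseen progression per patient who stops.

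- Stopping time uniform over 0 to 24 months: mean S(u) = 0.20 / (−ln 0.80) = 0.20 / 0.2231 = 0.896, so h = 0.896 − 0.800 = 0.096.
- Last PSA at one of the visits at 0, 3, …, 21 months, equally likely: mean S = 0.909, so h = 0.109.

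| Assumed share f | Bias, uniform stopping | Bias, last PSA at a visit | Bias if half are still found on time (half of the column before) |
| --- | --- | --- | --- |
| 5% | 0.5 points | 0.5 points | 0.3 points |
| 10% | 1.0 | 1.1 | 0.5 |
| 20% | 1.9 | 2.2 | 1.1 |
| 30% | 2.9 | 3.3 | 1.6 |

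A simulation of the visit-based version, with 400,000 patients per scenario, gave 80.5%, 81.1%, 82.1% and 83.4% under the stated rule for the four shares. With half of the progressions found on time it gave 80.2%, 80.6%, 81.1% and 81.6%. Censoring at the last PSA returned 79.9% to 80.1% throughout.

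**Prognostic factors.** Take a factor with no true effect, where 5% stop PSA in one group and 20% in the other. The visit-based estimates are 80.5% and 82.2%, and the apparent hazard ratio is ln 0.8218 / ln 0.8054 = 0.91. With 30% in the second group it is ln 0.8327 / ln 0.8054 = 0.85. These figures assume that no progression is found after PSA stops. For scale, two equal groups of 85 (an assumed split) at 80% give a standard error for the difference of √(2 × 0.16 / 85) = 6.1 points, well above the 1.6-point shift in the first contrast.

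**The case against.** The strongest reply is that PSA shares the 3-monthly clock with every other check, and the protocol describes no survival-only contact such as telephone calls or registry linkage. Last follow-up then most naturally means the last scheduled check, at which a PSA is due. For a patient who keeps the schedule, or who leaves the study altogether after a visit with a PSA, the two dates coincide and there is no bias. This stands, and it is why the point is conditional.

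It can also be said that the meaning of last follow-up belongs in the SAP. That holds in part. But the protocol itself fixes the censoring date for its primary endpoint, and an SAP that followed the words as written would carry the problem forward.

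Three stronger readings are tempting, and the documents do not support them:

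- **That progression cannot be seen at all once PSA stops.** Section 3.3 allows imaging for clinical progression, and death counts as an event.
- **That 5% of patients will behave this way.** The 5% in section 6.3 is a drop-out allowance for accrual, not a rate of stopping PSA while remaining in contact.
- **That patients have up to 84 months of survival contact after PSA ends.** The 84 months is the whole study, including 36 months of enrolment, and no separate survival phase is described.

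Finally, censoring at the last PSA is not free of assumptions: it is unbiased only if stopping PSA is unrelated to prognosis. That also stands.

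**Conclusion.** The point holds as a minor one. The stated censoring date is not tied to the assessments that reveal progression. Where the last contact falls after the last PSA, any progression missed in between can only raise the PFS estimate.

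The size depends on a share the protocol does not give. It is zero if every last contact includes a PSA, about 0.5, 1 and 2 points for assumed shares of 5%, 10% and 20%, and about half that if clinical imaging finds half of the progressions. Even at 30% the bias of about 3 points stays inside the planned 6-point margin. A reader might infer that the 2-year rate will be materially overstated; nothing in the protocol shows that.

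The prognostic comparison is the better reason to act, because differential PSA adherence would bias it and sample size would not help. That too needs a difference between groups that is only assumed here.

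**What to change.** In section 3.3, replace the censoring clause with wording such as: *patients without progression or death are censored at the date of the last PSA, or of imaging if later, that shows no progression.* State how a death after a gap of missed PSA assessments is counted, and run a sensitivity analysis with the alternative. Without that rule, counting such deaths as events while survivors are censored at their last PSA would add a downward bias. Keep the date of last contact as the censoring date for overall and cause-specific survival only.

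The cost is a sentence or two. PSA is already scheduled every 3 months, so no new data are needed, and the planned sample size does not change. Some patients will be censored earlier, so the interval widens slightly, and the new rule still relies on PSA stopping being unrelated to prognosis.

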**2. OVERVIEW OF STUDY DESIGN**

**2.1. Hypothesis:**

This observational study was designed to evaluate PFS after PSMA-PET/CT based salvage approach for patients affected by BR after RP.

- 1. **Study design**

This is a prospective observational multicenter study including patients treated with upfront RP +/- postoperative prostate bed radiotherapy, with histological result of Prostate adenocarcinoma, affected by BR (defined as PSA > 0.2 ng/ml) with a PSA at recurrence < 1 ng/ml. Patients will be staged with centralized 68Ga-PSMA PET/CT and treated with a pre-defined approach based on 68Ga-PSMA PET/CT findings, according to routine clinical practice:

| Negative 68Ga-PSMA PET/CT or positive findings within prostate bed | Prostate bed RT*, **, *** |
| --- | --- |
| 68Ga-PSMA PET/CT detecting pelvic nodal recurrence (defined as nodal disease < 2 cm under aortic bifurcation) amenable with stereotactic body radiation therapy (SBRT) on all sites of disease | SBRT to positive nodal disease |
| Abdominal nodal or bone oligometastatic disease (defined as < 3 non visceral lesions, according to Association of Radiotherapy and Clinical Oncology (AIRO) definition [D’angelillo 2019]) amenable with stereotactic body radiation therapy (SBRT) on all sites of disease | SBRT on all sites of disease |
| Abdominal nodal or bone metastatic disease (> 3 lesions or non-amenable with SBRT) and/or visceral disease. | ADT+/-other systemic therapies available for metastatic hormone sensitive pCa at physician discretion |

**For patients who did not previously received prostate bed RT, dose intensification (e.g 72-74 Gy in 36-37 fractions or equivalent dose/fractionation schedules) will be provided* *in case of positive PSMA/PET-CT findings inside prostate bed. In this case, Stereotactic Salvage RT (e.g. 35 Gy in 5 fractions on macroscopic recurrence) is allowed within site-specific study protocols.*

*** For patients who already received prostate bed RT in postoperative setting with negative findings within prostate bed, observation and PSMA-PET/CT re-staging at further PSA progression (defined as > 25% PSA increase if compared to PSA at recurrence) will be performed*

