**4. STUDY POPULATION**

**4.1. Inclusion Criteria**

Each potential subject must satisfy all of the following criteria to be enrolled in the study.

- Signed informed consent
- Age >18
- Patient suitable for 68Ga-PSMA PET/CT re-staging according to clinical practice (Previous radical prostatectomy with histological result of Prostate adenocarcinoma +/-postoperative prostate bed radiotherapy (adjuvant or salvage setting), with a biochemical relapse defined as a PSA > 0.2 and <1

1. **Exclusion Criteria**

- ADT administration within 6 months from studyenrollment
- Persistent elevation of PSA after RP measured within 16 weeks from surgery (> 0.1 ng/ml)

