**6.3 Statistical Analysis**

Considering the observational nature of the present protocol, a strict criterion for a target accrual would not be needed. However considering a reported rate for 2 year progression free survival after salvage radiotherapy alone of 80% [Carrie 2019], a sample size of 172 patients would be needed to estimate with a 6% precision margin and a 95% confidence interval. Considering a 5% drop out rate, 180 patient are the target accrual fixed for this study. In case this target could not be achieved, smaller sample size would lead to 95% confidence intervals ranging 73-86% (for N=150), 72-87% (for N=120), and 70-88% (for N=90), i.e. with a precision margin still within 10% (always assuming a 2-y PFS equal to 80%). Furthermore, considering that PSMA PET/CT has been shown to change therapeutic management in 34% of cases [DeAndreis 2020], 90 patients would be sufficient to assess with a 11% precision margins the rate of patients in whom re-staging allowed to tailor management. Considering the explorative nature of the translational objectives of the study, a target sample size will not be needed.

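### The primary PFS definition gives no usable time origin or nadir for patients managed by observation after earlier prostate-bed radiotherapy

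*Protocol*

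**What the plan says.** **Endpoint.** Protocol section 3.3 makes prognostic factors for 2-year PFS the primary endpoint. The clock starts when the salvage therapy given for the first relapse ends. The PSA component has two branches. The first reads: "Biochemical progression is defined as the date in which a PSA increase above 0.2 ng/ml for patients with a PSA nadir < 0.2 ng/ml". The second, for a nadir above 0.2, asks for two successive rises of more than 25% over nadir. The section does not say from when the nadir is counted.

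**Who is enrolled.** Section 4 admits patients with PSA above 0.2 and below 1, with or without earlier bed radiotherapy (adjuvant or salvage). It excludes "Persistent elevation of PSA after RP measured within 16 weeks from surgery (> 0.1 ng/ml"), so every enrolled patient should have had a PSA of at most 0.1 soon after surgery. Section 3.1 addresses the cohort as enrolled.

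**Who is observed.** The footnotes to the management table in section 2 say that, after earlier bed radiotherapy and with no finding in the bed, "observation and PSMA-PET/CT re-staging at further PSA progression (defined as > 25% PSA increase if compared to PSA at recurrence) will be performed". With a finding in the bed, observation is one of two options left to the clinician.

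**Planning value.** Section 6.3 relies on "a reported rate for 2 year progression free survival after salvage radiotherapy alone of 80" per cent, and continues: "a sample size of 172 patients would be needed to estimate with a 6% precision margin and a 95% confidence interval". It then adds: "Considering a 5% drop out rate, 180 patient are the target accrual fixed for this study".

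**The concern.** An observed patient completes no salvage treatment in this study, so the PFS clock has no start. Read literally, a patient relapsing after an earlier salvage course would start the clock at the end of that course, before enrolment. The PSA rule has the same gap, because it is tied to a nadir that observed patients have only before entry or as an untreated starting value.

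This matters because the study's main aim is prognostic. Earlier bed radiotherapy decides who can be observed, and observation decides how the endpoint behaves. An association between earlier radiotherapy and 2-year PFS could then come partly from the rule rather than from the disease. Sites could also date the same patient's event differently. Finally, the 80% behind the sample size describes patients given salvage radiotherapy, whereas the cohort also contains observed patients and patients given ADT.

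**Working it through.** **1. The plan's own figures.** Inputs from section 6.3: p = 0.80, margin d = 0.06, 95% confidence, 5% dropout.
- n = 1.96² × 0.80 × 0.20 / 0.06² = 170.7, so 171 (stated 172).
- 171 / 0.95 = 180; 172 / 0.95 = 181.1, so 182 (stated 180).
- The fallback intervals, "95% confidence intervals ranging 73-86% (for N=150), 72-87% (for N=120), and 70-88% (for N=90"), match Clopper-Pearson limits: 72.7–86.1%, 71.7–86.7% and 70.2–87.7%.

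The arithmetic is sound. The question is what it describes.

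**2. The endpoint applied to an observed patient.**

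| Reading of origin and nadir | Result |
| --- | --- |
| Origin needs a salvage treatment in this study | PFS undefined |
| Origin is an earlier salvage course with nadir below 0.2 | Entry PSA above 0.2 is already an event |
| Nadir may be the post-surgery value (at most 0.1) | Entry PSA above 0.2 is already an event |
| Nadir counted from entry | Nadir above 0.2 while PSA rises; only the second branch applies |

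**3. The last reading in time.** Assume exponential growth with doubling time T months, the entry PSA as nadir, and 3-monthly values. A 25% rise takes T × log2(1.25) = 0.322 T months.
- *Two consecutive values each more than 25% above nadir.* The first must occur by month 21: T < 21 / 0.322 = 65 months. The event falls at month 6, 9, 12, 15 or 24 for T = 6, 12, 24, 36 or 60.
- *Two rises that must compound*, to 1.25² = 1.5625 times nadir: T < 24 / 0.644 = 37 months.
- *Each 3-month step itself above 25%*: T < 3 / 0.322 = 9.3 months; slower rises never count.

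**4. Effect on the pooled rate.** The protocol gives neither the observed share f nor the 2-year PFS q of observed patients. Both are assumptions here, and all other patients are taken at 80%.

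Pooled PFS = 0.80(1 − f) + q f; half-width at N = 172 is 1.96 × √(p(1 − p)/172).

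| q | f = 5% | f = 10% | f = 20% | f = 30% |
| --- | --- | --- | --- | --- |
| 0 | 76% (6.4) | 72% (6.7) | 64% (7.2) | 56% (7.4) |
| 0.2 | 77% (6.3) | 74% (6.6) | 68% (7.0) | 62% (7.3) |
| 0.4 | 78% (6.2) | 76% (6.4) | 72% (6.7) | 68% (7.0) |
| 0.6 | 79% (6.1) | 78% (6.2) | 76% (6.4) | 74% (6.6) |

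Half-widths in points are in brackets. The pooled rate drops more than 6 points once f exceeds 0.06 / (0.80 − q): 7.5%, 10%, 15% or 30% for q = 0, 0.2, 0.4 or 0.6. The half-width cannot exceed 1.96 × √(0.25/172) = 7.5 points. Holding 6 points at 72% would need 216 patients, or 228 with 5% dropout.

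**The case against.** The strongest reply is that the protocol never says observed patients receive a PFS time. The phrase about the enrolled cohort belongs to a general objective, analysis sets are usually settled in an SAP, and the nadir reads most naturally as post-treatment. It stands that inclusion is inferred from silence and that an event at entry is only one reading. It does not remove the point: the time origin is fixed in section 3.3 itself, and on the natural reading it leaves a planned subgroup with no PFS at all.

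Several stronger conclusions are tempting, and the documents do not support them:
- *Observed patients will progress within months.* This depends on doubling time and on how the two rises are counted.
- *The pooled rate will fall outside 80% ± 6%.* This depends on f and q, which are not given. The 80% is a planning value, not a hypothesis, and section 6.3 already tolerates margins up to 10%.
- *The 25% rule in the footnote is a rival endpoint.* It triggers re-staging; section 3.3 alone defines biochemical progression.
- *Any lesion on that re-staging PET counts.* Section 3.3 requires a new one.
- *ADT makes metastatic findings look favourable.* No figure in the protocol bears on this.
- *The radiotherapy group should become the primary estimate.* That would change the question, since the study sets out to evaluate a PET-based approach with several management routes.

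**Conclusion.** The point holds as a gap in the definition of the primary endpoint. For patients observed after earlier bed radiotherapy, section 3.3 yields either no PFS, an event on or before entry, or an event by 2 years for doubling times up to about 65, 37 or 9 months. That spread comes from one sentence being open to three readings. A prior-radiotherapy effect on 2-year PFS may therefore be partly an artefact of the rule.

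The numerical effect is conditional on f and q. The loss of precision is modest, from 6 points to at most 7.5; the larger harm is to what the pooled estimate and the prognostic model mean. It should be fixed, but it does not invalidate the sample-size arithmetic or the study.

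**What to change.** 1. In section 3.3, count PFS and nadir from the end of the PET-directed treatment given in this study. State a separate origin and nadir window for observed patients, for example from the date of the baseline PET, and say how the two consecutive rises are counted.
2. Report 2-year PFS by management group (PET-directed radiotherapy, observation, ADT) alongside the pooled figure. Do not read the prior-radiotherapy effect from the pooled model without accounting for management group.
3. Reconcile the PSA trigger for repeat PET in the section 2 footnote with the one in section 6 (evaluation during treatment), which uses the section 3.3 rule. Which applies is a clinical matter for the investigators.
4. In section 6.3, state that the 6% margin assumes 80% in the pooled cohort and could be about 6.5 to 7.5 points at lower rates, with the observed share and its PFS given as assumptions.

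The cost is protocol wording and one stratified table. The downside is wider intervals in smaller groups: at 80%, setting apart 10%, 20% or 30% of 172 leaves about 155, 138 or 120 patients and margins of 6.3, 6.7 or 7.2 points.

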**** For patients who already received prostate bed RT in postoperative setting with positive findings within prostate bed, both observation and PSMA-PET/CT re-staging at further PSA progression or prostate bed retreatment (e.g SBRT for a total dose of 30 Gy in 5 fractions) will be allowed according to clinician choice*

Planned size of the overall study population is 180 patients. Data about demographics, PSA, comorbidities and current drug therapies up to 45 days prior to enrollment will be collected at baseline. The study will consist in the observation of outcomes after 68Ga-PSMA PET/CT staging and following postoperative tailored management. Total planned duration of the study is 84 months, consisting in 36 months enrollment period and a later phase of 48 months in which patients will continue to be submitted to periodic checks every 3 months.

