**5. STUDY PROCEDURES**

Patients will be observed after management in order to record clinical outcomes and explore prognostic factors in this cohort. According to clinical practice, the following guideline will be adopted for prostate bed RT and SBRT on all sites of disease (pelvic nodal or oligometastatic)

*1: Prostate bed RT*

Postoperative RT to prostate bed will be administered in case of negative PET PSMA findings or positive findings within prostate bed. Clinical Target Volume (CTV) will be defined according to EORTC guidelines [Poortmans 2007], a CTV to Planning Target Volume (PTV) margin of 5-8 mm will be added according to clinical practice and Image guidance protocols adopted. Both 3D conformal or Intensity modulated RT /Volumetric Modulated Arc Therapy (3D CRT or IMRT/VMAT) are allowed, provided that at least 66 Gy in 33 fractions, or equivalent dose/fractionation schedules, are delivered. Dose intensification (e.g 72-74 Gy in 36-37 fractions or equivalent dose/fractionation schedules) will be provided in case of positive PSMA/PET-CT findings inside prostate bed. At least 95% of PTV should be covered by 95% prescription isodose. Less than 10% of the PTV should be higher than the 105% prescription isodose. Dose constraints to Organs at risk (OAR) should respect QUantitative Analysis of Normal Tissue Effects in the Clinic (QUANTEC) report [Marks 2010]. In case of positive findings within prostate bed in patients who did not received postoperative prostate bed RT, Stereotactic Salvage RT (e.g. 35 Gy in 5 fractions on macroscopic recurrence) is allowed within site-specific study protocols.

*2: SBRT on all sites of disease (pelvic nodal or oligometastatic)*

The GTV will be any demonstrable abdominal nodal or bone metastatic disease detected by PSMA PET/CT. Morphological, topographical and metabolic informations should be integrated to delineate the target volumes. Rigid or deformable co-registration is allowed. No CTV is allowed for SBRT treatments. A GTV to PTV margin of 3-5 mm will be added according to clinical practice and image guidance protocols adopted.

The following dose/fractionation schedules could be adopted to perform SBRT:

| Total dose (Gy) | Dose per fraction (Gy) | Number of fractions |
| --- | --- | --- |
| 24 | 8 | 3 |
| 27 | 9 | 3 |
| 30 | 10 | 3 |
| 36 | 12 | 3 |
| 30 | 6 | 5 |
| 35 | 7 | 5 |
| 40 | 8 | 5 |
| 45 | 9 | 5 |
| 36 | 6 | 6 |
| 45 | 7.5 | 6 |

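### Radiological PFS counts only new lesions, so failure in a lesion already seen on the index PSMA PET/CT is not an event, while the same failure in a PET-negative patient is

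*Protocol*

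**What the plan says.** Section 3.3 of the protocol lists among the secondary endpoints "Radiological PFS, defined as the occurrence of any new lesion detectable with PSMA" PET/CT or another molecular or radiological exam. The exam is one "which will be performed in case of biochemical or clinical progression". The entry names no other event, no start date and no censoring rule.

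The primary endpoint in the same section uses the same event for its radiological component: "Radiological progression will be defined as the occurrence of any new lesion detectable with PSMA PET/CT and/or any other molecular/radiological exam". Primary PFS as a whole is wider. It runs from the end of salvage treatment to "documented biochemical progression or radiological progression (or both), death from any cause or censoring at date of last follow-up".

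Management follows the index PET result (section 2, Study design table and footnotes; section 5):

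- **Prostate bed:** "Postoperative RT to prostate bed will be administered in case of negative PET PSMA findings or positive findings within prostate bed".
- **SBRT:** the target is the lesion that PET showed: "The GTV will be any demonstrable abdominal nodal or bone metastatic disease detected by PSMA PET/CT".
- **Systemic therapy:** this group also has known lesions: "Abdominal nodal or bone metastatic disease (> 3 lesions or non-amenable with SBRT) and/or visceral disease".
- **Positive bed after earlier bed radiotherapy:** the footnote allows "both observation and PSMA-PET/CT re-staging at further PSA progression or prostate bed retreatment", so a known lesion may be left untreated.

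No other section widens or corrects the new-lesion wording.

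**The concern.** A PET-positive patient enters follow-up with at least one documented lesion, and a PET-negative patient with none. A rule that counts only new lesions therefore applies differently to the two groups. It cannot register recurrence or growth at the site that was treated because PET showed it, but it registers a first lesion at the same site in someone whose scan was clear.

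The endpoint exists to explore prognostic factors. The protocol does not list candidate factors, but index PET status, or site of PET disease, is an obvious one in a study whose management is set by PET. If the event definition itself depends on PET status, a comparison by PET status partly reflects the definition rather than the disease.

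Separately, an endpoint called PFS that does not name death differs from the protocol's own use of the term a few lines above it.

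**Working it through.** **1. No stated figure to reproduce.** The protocol gives no rate or sample size for radiological PFS. Section 6.3 covers primary PFS, the rate of management change, and the statement that the translational objectives need no target size. The point rests on wording; the numbers below only illustrate it.

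**2. The same failure under the written rule.**

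| Later finding | Index PET negative | Index PET positive at that site |
|---|---|---|
| Lesion in the irradiated prostate bed | New: event | Already known: not an event |
| Recurrence or growth in an SBRT-treated node or bone lesion | No known lesion exists; any lesion there is new: event | Already known: not an event |
| Growth of a positive bed under observation | Not applicable | Already known: not an event |
| Lesion at a fresh site | Event | Event |

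Leaving out a type of event can only raise the event-free proportion. Recurrence or growth of a known lesion is possible only in PET-positive patients, so this omission works in one direction between the groups.

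**3. Size by direct count (assumed rate).** Suppose a proportion of PET-positive patients fail only in a known lesion. By definition they have no new lesion, so the written rule counts all of them as event-free. At an assumed 5-10%, the event-free proportion is overstated by 5-10 points in PET-positive patients and, from this source, by 0 in PET-negative patients. At 0% there is no difference.

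**4. Deaths (assumed rate).** At 2 years, the horizon of the primary endpoint, with N = 180 (section 6.3):

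- 1% per year: 1 - exp(-0.01 x 2) = 1.98%; x 180 = 3.6
- 2% per year: 1 - exp(-0.02 x 2) = 3.92%; x 180 = 7.1

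That is about 4-7 patients. Nothing in the protocol shows that the rate differs by PET status.

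**5. Effect on a comparison (all rates assumed).** Let a, r and d be the 2-year probabilities of a new lesion, of failure in a known lesion and of death, acting independently. Set a = 10% or 20% in both groups, d = 1.98% or 3.92% in both, and r = 0 in PET-negative patients. The event-free proportion is 1 - a under the written rule and (1 - a)(1 - r)(1 - d) when all three count.

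Example with a = 10%, r = 5%, d = 1.98%:

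- PET-negative: 0.90 x 0.9802 = 0.882, against 0.900 as written (1.8 points)
- PET-positive: 0.90 x 0.95 x 0.9802 = 0.838, against 0.900 as written (6.2 points)
- Hazard ratio, PET-positive to PET-negative: ln(0.838)/ln(0.882) = 1.41, against 1.00 as written

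| r in PET-positive | Overstated, PET-negative | Overstated, PET-positive | Difference | Hazard ratio, all events (1.00 as written) |
|---|---|---|---|---|
| 0% | 1.6-3.5 points | 1.6-3.5 points | 0 | 1.00 |
| 5% | 1.6-3.5 points | 5.5-7.9 points | 3.8-4.4 points | 1.2-1.4 |
| 10% | 1.6-3.5 points | 9.4-12.2 points | 7.7-8.8 points | 1.4-1.8 |

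The differences are a little below the 5-10 points of step 3 because here some patients with failure in a known lesion also develop a new one and so are counted anyway.

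**6. Primary PFS.** Imaging is triggered by biochemical or clinical progression (section 3.3; section 6, Evaluation During Treatment). A failure in a known lesion that is found because PSA progressed is already a primary event, and death counts too. The remaining gap is clinical progression without PSA progression.

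**The case against.** **Death and start date may be inherited.** The occurrence of a lesion is an event, not a time, so the entry cannot be a complete time-to-event definition. It can be read as primary PFS restricted to its radiological component, with the same origin, death rule and censoring. That reading is reasonable, and such detail is often left to an SAP, which has not been seen here. A reader might infer that deaths are to be censored; the protocol does not say so. What stands is that death is not named and should be.

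**A reappearing treated lesion might be called new.** The wording does not support this, and centres that read it differently would score the same scan differently. Inheritance from primary PFS does not help, because its radiological component uses the same new-lesion wording.

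**The size is assumed.** This is correct. No rate of failure in known lesions is given, and at zero the groups do not differ. A reader might also apply the death rate to the whole study: a mean of 48 + 36/2 = 66 months (5.5 years) gives 10-19 deaths. That takes every patient to month 84, ignores the planned 5% drop-out and goes beyond the only PFS horizon the protocol states, which is 2 years.

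**The endpoint is exploratory.** It is one of several secondary endpoints in an observational cohort, with no test or sample size attached, and local control is not a stated objective. This limits the weight of the point. It does not remove it, since exploring prognostic factors is the declared use and the rule scores failure by a likely factor.

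**Conclusion.** The point holds for the secondary endpoint. The protocol does not merely leave detail open; it fixes an event rule under which recurrence or growth of a known lesion never counts, whereas a lesion at the same site in a PET-negative patient does. The direction follows from the wording: if any patients fail only in a known lesion, radiological PFS is overstated in PET-positive relative to PET-negative patients.

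The size is unknown. The 5-10 points and the hazard ratios above depend wholly on assumed rates, as do the 4-7 deaths at 2 years. The death omission is a smaller matter of clarity, with no shown difference by PET status.

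Two stronger conclusions are tempting and not supported. One is that PET-positive results are shown to be biased by a known amount; the documents contain no rate from which to say so. The other is that primary PFS is compromised; it also counts PSA progression and death, so it is largely protected, and aligning its radiological wording is a matter of consistency.

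**What to change.** Define radiological PFS in section 3.3 as the time from the end of salvage treatment, with the same origin and censoring as primary PFS, to the first of:

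- a new lesion;
- recurrence or progression of a lesion present on the index scan, including inside the irradiated volume, judged against the index scan by a stated criterion;
- death from any cause.

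Use the same radiological wording in primary PFS, and report in-field and out-of-field failure separately.

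Keeping the end-of-treatment origin matters because primary PFS and the section 3.3 definitions of overall and cause-specific survival start there. Patients managed by observation have no such date, so the shared origin should be stated for them as well.

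**Cost.** No extra visits or scans are needed, since PSMA PET/CT at biochemical progression is already planned. It is more than a change of wording in one respect: a criterion for progression of a known lesion has to be written, and no routine post-treatment scan is planned as a reference, hence the comparison with the index scan. Reported radiological PFS will be less favourable than under the present definition if any such failures or deaths occur.
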